### Secondary clinical outcome measures

#### Perioperative outcome measures

We will record operative time (minutes from first incision to closure), blood loss (millilitres), and the time and total radiation dosage used during fluoroscopy (millisieverts). Regarding fluoroscopy, any variations from confounders will be recorded and reported.

#### Postoperative outcome measures

Additional objectives of the study include comparing the effect of surgical outcomes; postoperative outcome measures include:Tibial alignment from post-operative lateral and anteroposterior radiographs (all follow-up time-points),Time to union as indicated on post-operative radiographs,Rotational profile from MRI (6 and 12 months follow-up),Intra-articular damage from MRI (6 and 12 months follow-up),Subsequent surgeries and complication rate (e.g. compartment syndrome, surgical site infection, malunion, nonunion, screw penetration in the tibiofibular joints),Fracture location will also be recorded as this may influence outcomes.

#### Clinical assessment

At each follow-up, a clinician will assess lower extremity function including a general clinical assessment of tenderness, swelling, and range of motion, and record the Knee Society Score [44] (KSS). The KSS is a widely used system to score the function of the knee, comprising two parts: (1) the Knee Score (KS-KS) and (2) the Function Score (KS-FS). The scores range from 0 to 100; a higher score is equivalent to a better outcome. The Minimal Clinically Important Difference (MCID) for the KS-KS ranges from 5.3–5.9 points and for the KS-FS from 6.1–6.4 points [45].

#### Patient reported outcome measures

PROMS will be captured electronically at 3, 6, 12, and 18 months follow-up.

##### Knee injury and osteoarthritis outcome score [16] (KOOS)

The KOOS has been validated for osteoarthritis [16] and for knee arthroplasty [46]. A normalised score between 0 and 100 (0 representing extreme knee problems and 100 representing no knee problems) for each of the five subscales is calculated. The MCID for the KOOS has not been assessed. Importantly, the KOOS contains a question relating to kneeling.

##### KOOS patellofemoral subscale [47] (KOOS-PF)

The KOOS-PF contains 11 items that generate a normalised score from 0 to 100, similar to the KOOS. The subscale was developed for AKP/patellofemoral pain and/or patellofemoral osteoarthritis. The KOOS-PF is suitable to be used in conjunction with the KOOS [47]. The MCID for the KOOS-PF is 11.8 [47].

##### Functional joint Score-12 knee [48] (FJS-12 knee)

The FJS-12 Knee contains 12 items scored from 1 to 5. The raw score is normalised to 0–100, where a high score indicates a good outcome. The FJS-12 Knee displays low ceiling effects in more active and younger patient groups [49]. The FJS-12 Knee has been validated for anterior cruciate ligament reconstruction [49] and knee arthroplasty [50].

##### Quality of life (via EuroQol 5-dimension 5-level (EQ-5D-5L) [51])

The EQ-5D-5L is a standard instrument used to assess general health outcomes, comprising the EQ-5D descriptive system and the EQ visual analogue scale (EQ VAS). The descriptive system comprises 5 dimensions each with 5 levels. The EQ VAS is scored from 0 to 100. EQ-5D-5L provides stronger validity evidence than the EQ-5D-3L for osteoarthritis [52] and has been previously used in IM nail studies [53–55].

##### Visual analogue scale [56] (VAS)

The VAS is a longitudinal scale ranging from 0 to 10 centimetres, zero indicating no pain, and ten indicating the worst pain imaginable. Patients will be asked to score their usual pain for the last week. The MCID for VAS scores is 2 points or 2 cm [56]. VAS is suitable to be administered electronically [57–60].

##### Pain Catastrophizing scale [61] (PCS)

The PCS is a 13-item questionnaire scored from 0 to 4 that provides a valid index of catastrophizing of pain. The total score ranges from 0 to 52. A higher score is associated with more catastrophic thinking. There is no MCID available for the PCS.

#### Covariates

##### New mobility score [41] (NMS)

The NMS contains three items pertaining to patients’ ability to walk indoors, outdoors, and go shopping. Each item is scored from 0 to 3, resulting in a score from 0 to 9, where nine indicates a high level of mobility.

##### Medication

Patients will be asked to detail any current medication at all follow-ups.

##### Rehabilitation

Patients will be asked to detail the number of physiotherapy appointments they have recently attended at all follow-ups.

##### Return to work

As time from surgery as indicated at any of the follow-up time-points. We will also record any changes to occupation or working capacity resulting from the leg injury or from AKP.

#### Performance based outcome measures

PBOMS will be conducted at 3, 6, 12, and 18 months follow-up. Three-dimensional (3-D) kinematic data will be captured with a 10-camera motion capture system (Vicon Motion Systems Ltd, Oxford, UK, 100 Hz) in line with standardised protocols [62]. Ground reaction forces will be captured using two in-ground force platforms (AMTI Optima, Watertown, MA, USA, 2000 Hz). Lower extremity muscle activity will be measured using passive surface electromyography electrodes (Delsys, Boston, MA, USA, 2000 Hz). A custom Matlab user-interface (MathWorks, Natick, MA, USA) and Vicon Nexus 2.9 (Vicon Motion Systems Ltd, Oxford, UK) will be used for data capture. Musculoskeletal modelling using OpenSim [63] will simulate gait parameters including (but not limited to) knee kinematics, knee joint contact forces, and knee muscle forces.

In addition to walking gait at self-selected speed, participants will conduct a series of performance-based functional tests to generate data related to AKP, knee function, and thigh muscle performance, including:Maximum isometric thigh muscle strength recorded with a MicroFET2 digital handheld dynamometer (HOGGAN Scientific, Salt Lake City, UT, USA) [64];Kneeling ability assessed using:Aberdeen Weight-Bearing Test (Knee) [33] (AWT-K) in upright and flexed positions. The AWT-K tests for anterior knee discomfort using the ratio of weight distribution between both legs during kneelingKneeling range of motion reaching tasks similar to previously described in literature [65]The effect of cushioning using Mechanix Wear 700 Series knee pads (Mechanix Wear, Valencia, CA, USA)The anatomic structures in contact with the ground during these kneeling assessments will be determined using a combination of eight force sensitive resistors (Delsys, Boston, MA, USA) arranged about the patella similar to previously described in literature [65]‘Timed up and go’ test [66];Single-legged anterior reach test [67];Timed seated leg extension hold;Squatting;Anterior single-legged, single hop-for-distance test [67];Step up/over test [68] and step down test [69].

Twenty-four-hour physical activity patterns will be recorded for 7 days following gait-lab sessions using a wrist-worn activity monitor (GeneActiv Original, Activinsights Ltd, Kimbolton, UK, 100 Hz). Patients will be asked to keep a sleep log to differentiate sedentary and sleep time. Physical activity captured using wrist-worn accelerometers on either wrist strongly correlates with devices worn around the waist but are less obtrusive [70].

An overview of all data collection at all time-points is presented in Table 1.

**Table 1 Tab1:**
[figure not shown]
Overview of data collection from intervention to 18-months follow-up

*Captured retrospectively after discharge

*NMS* New Mobility Score, *KSS* Knee Society Score, *ROM* range of motion, *PROMS* patient reported outcome measures, *KOOS* Knee Injury and Osteoarthritis Outcome Score, *KOOS-PF* KOOS patellofemoral subscale, *FJS-12 Knee* Functional Joint Score-Knee, *EQ-5D-5L* EuroQoL 5-Dimension 5-Level, *PCS* Pain Catastrophizing Scale, *VAS* visual analogue scale, *PBOMS* performance based outcome measures, *MIQS* maximum isometric quadriceps strength, *TUG* timed up-and-go

### Exploratory clinical outcomes

The tertiary objective of this study is the development of novel outcome measures specific to IM nailing of tibial shaft fractures from a series of performance-based and patient-reported outcomes captured in the pilot RCT. The successful development of the new tool using a combination of PROMs and PBOMs will be assessed on its ability to differentiate participants with and without AKP.

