### Tertiary objectives

The tertiary objective of the study is to explore the development of novel three-dimensional (3-D) motion capture based biomechanical outcome measures for assessing AKP and knee function after tibial fracture surgery. This will be achieved by evaluating objectively measured biomechanical outcomes and gait patterns against patient-reported outcome measures of knee pain and function.

Additional objectives include comparing the effect of SPN versus IPN on surgical outcomes including: tibial alignment, rotational profile, intra-articular damage, and time to union.

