### Primary clinical outcome measure

The primary clinical outcome measure for the pilot RCT is the incidence of AKP at 12-months follow-up. To assess AKP, participants will be asked to answer the following questions:

1. Do you experience any pain in the knee of the leg that was operated on? Yes/No

2. Was this pain present only after surgery and not beforehand? Yes/No

3. Is this pain located over the front of your knee? Yes/No

If patients answer yes to all questions, their pain will be regarded as postoperative AKP.

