As this is a pilot study, any analyses related to the clinical outcomes should be treated with caution and viewed as exploratory. All clinical outcome measures will be assessed descriptively (means and standard deviations for normally distributed continuous variables; medians and interquartile ranges for non-normal continuous variables; frequencies and percentages for categorical variables). Missing data will be tabulated.

Logistic regression models will be used to determine the association between surgical approach and AKP 12 months post-surgery. Models will be adjusted for age and gender with hospital included as a fixed effect. The results will be reported as odds ratios with 95% confidence intervals.

Secondary clinical outcomes will be analysed using linear regression models for continuous outcomes or generalised linear models for count or categorical outcomes. Generalised estimating equations will be used to account for correlation due to repeated measures over time, and a time-by-surgery interaction term will be included to test for differences in the relationship between surgical approach and outcomes over time. If assumptions about distributions are not met (e.g. non-normally distributed continuous outcomes) alternative approaches will be explored as appropriate, including transformations or non-parametric modelling.

To assess differences between cases and matched healthy controls, logistic regression models will be used to determine the association between treatment (surgery versus no surgery) and AKP 12 months post-surgery. Models will be adjusted for the matching variables age, gender, and body mass index, with hospital also included as a fixed effect.

To determine novel predictors of functional outcomes, logistic regression prediction models will be used to assess the discriminatory power of PROMs and PBOMs at assessing AKP and other functional measures. Estimates of discrimination (area under the curve, sensitivity, and specificity) will be used to rank combinations of outcomes in ability to predict AKP. Principal component analysis (PCA) will be explored as a method of data reduction to allow information from a larger number of variables to be included in the predictive model. If PCA is successful, a predictive model will be fitted using an appropriate number of principal components (determined using the proportion of variance explained as well as number of events in the dataset) as predictors.

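### The combined PROM and PBOM tool is assessed on separating self-reported AKP, so good discrimination can come from the PROMs alone and would not show that motion capture detects AKP

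*Protocol article*

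**What the plan says.** All places are in the protocol article.

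- **Tertiary objectives.** The aim is to "explore the development of novel three-dimensional (3-D) motion capture based biomechanical outcome measures for assessing AKP and knee function after tibial fracture surgery". The route is "evaluating objectively measured biomechanical outcomes and gait patterns against patient-reported outcome measures of knee pain and function". Here the PROMs are the yardstick.
- **Exploratory clinical outcomes.** The "new tool using a combination of PROMs and PBOMs will be assessed on its ability to differentiate participants with and without AKP". Here the PROMs are part of the tool.
- **Primary clinical outcome measure.** AKP is yes to all three self-report questions. The first is "Do you experience any pain in the knee of the leg that was operated on? Yes/No", the third is "Is this pain located over the front of your knee? Yes/No", and the second asks whether the pain began only after surgery.
- **Patient reported outcome measures.** Collection is at 3, 6, 12 and 18 months. Of the KOOS-PF the protocol says: "The subscale was developed for AKP/patellofemoral pain and/or patellofemoral osteoarthritis". The list also holds the KOOS and a VAS for usual pain in the last week.
- **Statistical analysis.** Logistic prediction models use PROMs and PBOMs. AUC, sensitivity and specificity "will be used to rank combinations of outcomes in ability to predict AKP". Principal components may serve as predictors. No PBOM-only model and no measure of added value over PROMs is named.
- **Abstract and Discussion.** Whether motion analysis can register AKP after nailing is listed as a limitation that is still unknown.

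**The concern.** Predictors and outcome share content. A patient who reports knee pain in the AKP questions will tend to report it in the KOOS-PF, KOOS and VAS as well. A tool that contains those scores can separate patients with and without AKP whether or not the gait-laboratory data carry information, and ranking by AUC will tend to favour the sets that contain pain PROMs.

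What is at stake is how the result is read. The Background argues that PROMs alone are not enough, and expects biomechanically validated measures to be used in a full-scale trial. A high AUC for the combined tool could be taken as support for the biomechanical part when it says nothing about it. A larger sample or better internal validation would not cure this, because the problem lies in what is being assessed.

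**Working it through.** The protocol gives no figure on this point (no AUC target or threshold), so there is none to reproduce.

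**Step 1: the roles of the PROMs.** Under Tertiary objectives they are the comparator for biomechanics. Under Exploratory clinical outcomes they are components of the tool, and the comparator is AKP. A measure cannot be both the yardstick and part of what is measured if the question is whether the remaining part works.

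**Step 2: can the assessment look good with no signal from PBOMs?** Inputs from the protocol:
- Completers: 25 per group, 50 in total (Sample size).
- AKP rate: 47%, the meta-analysis average in the Discussion. 0.47 × 50 = 23.5, taken as 24 with AKP and 26 without.

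Assumptions, not in the protocol:
- One normally distributed PROM with a set true AUC. Its mean shift is d = √2 × Φ⁻¹(AUC); for AUC 0.90, d = 1.414 × 1.282 = 1.81.
- 1, 3 or 5 PBOMs with no information (true AUC 0.50).
- A logistic model with a negligible ridge penalty, 1000 simulated trials per setting; the first 100 were also scored on new data.

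Mean AUC with 1 / 3 / 5 uninformative PBOMs:

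| Assumed PROM AUC | Combined, in sample | Combined, new data | PBOM-only, in sample |
|---|---|---|---|
| 0.50 | 0.600 / 0.651 / 0.691 | 0.500 / 0.499 / 0.500 | 0.564 / 0.628 / 0.673 |
| 0.70 | 0.717 / 0.745 / 0.771 | 0.679 / 0.661 / 0.645 | 0.563 / 0.629 / 0.675 |
| 0.80 | 0.808 / 0.828 / 0.846 | 0.787 / 0.772 / 0.752 | 0.566 / 0.627 / 0.675 |
| 0.90 | 0.904 / 0.918 / 0.927 | 0.894 / 0.880 / 0.868 | 0.565 / 0.633 / 0.676 |
| 0.95 | 0.953 / 0.961 / 0.968 | 0.946 / 0.935 / 0.924 | 0.564 / 0.630 / 0.675 |

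PBOM-only AUC on new data was 0.497 to 0.502 throughout. With an informative PROM the combined figure follows the PROM, although the PBOMs contribute nothing.

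**Step 3: what would tell the cases apart?** PBOM-only AUC and the gain over PROMs do so, but only after correction for optimism. At PROM AUC 0.90 with three null PBOMs, the in-sample gain is 0.918 − 0.901 = +0.017, while on new data it is 0.880 − 0.90 = −0.020. The PBOM-only AUC is 0.633 in sample and 0.499 on new data.

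**Step 4: precision.** For an uninformative score, SE(AUC) = √[(24 + 26 + 1) / (12 × 24 × 26)] = √(51/7488) = 0.083, so the 95% half-width is 1.96 × 0.083 = 0.16. A PBOM-only estimate from this pilot will be imprecise and needs its interval.

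**The case against.** The protocol can be defended on several grounds.

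- **No verdict is defined.** The tool is to be assessed on discrimination; there is no threshold or pass/fail rule. This stands. A reader might infer that the tool will be declared successful, but the text does not say so.
- **A combined tool is intended.** The Background argues that both kinds of measure are needed, and nowhere claims that the combined AUC proves motion capture works. This is fair, but the tertiary objective is stated as motion-capture measures, and no other assessment of the new tool is fixed.
- **The ranking may already give the answer.** Combinations could include PBOM-only and PROM-only sets, and the models also address other functional measures. This stands as a possibility. It is not stated, and the criterion for the tool does not require it.
- **This is not incorporation of the reference standard.** A reader might infer that it is. The three AKP questions are not among the listed PROMs, and AKP also needs an anterior site and onset after surgery, whereas the VAS as described names no site. Content overlap is the accurate term, and its strength is not known from the document.
- **The illustration assumes its inputs.** This stands. Nor is it true that a combination always does at least as well as the PROM alone: that holds for ideal weights, whereas the fitted models fell slightly below it on new data.
- **Progression does not depend on the tool.** This stands. Table 2 uses enrolment, retention, compliance and adverse events, so the documents do not support the inference that a high combined AUC would commit the full trial to gait-laboratory testing.
- **Model detail belongs in the analysis plan.** This is true of model specification. The criterion itself, and the conflict over the role of the PROMs, are in the article.

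**Conclusion.** The point holds as a mismatch between the tertiary objective and the way the new tool is assessed. Good discrimination by the PROM and PBOM combination can come from the PROMs alone and does not show that motion capture detects AKP. With assumed PROM AUCs of 0.80 to 0.95 and uninformative PBOMs, the combination still reaches 0.75 to 0.95 on new data, against about 0.50 for PBOMs alone. These figures show the mechanism and do not forecast the trial's result. The conclusion needs only that the pain PROMs discriminate self-reported AKP well; if they did not (PROM AUC 0.50), the combination would also fail on new data. The weight is moderate: the aim is exploratory and no trial decision is tied to it, but the change is cheap and bears on an unknown that the protocol itself names.

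**What to change.** Reconcile Tertiary objectives, Exploratory clinical outcomes and Statistical analysis on whether PROMs are the comparator or part of the tool. Then state that the motion-capture component will be assessed by:

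1. discrimination of AKP by PBOM-only models, or by principal components derived from PBOMs only; and
2. the gain in AUC when PBOMs are added to a PROM-only model that includes the KOOS-PF and pain VAS.

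Report both with confidence intervals and optimism correction (for example by bootstrap). If principal component analysis is used, run it separately on PROMs and PBOMs so that the sources stay distinguishable. Keep the combined model as descriptive, and do not cite its AUC as evidence that the biomechanical measures work.

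The cost is slightly more analysis on data already planned, with no new assessments. The headline discrimination will look less favourable, and with about 50 completers the intervals will be wide.

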### Protocol deviations

Patients that undergo nail removal will be asked to be followed up for an additional 18 months after nail removal. Indications for nail removal may include patient preference, knee pain, and infection [71].

### Data management

All questionnaire data, except for the KSS and sleep logs, are captured electronically. The KSS is captured on paper by the treating clinician at the clinical reviews; the sleep logs are captured on paper by the participants. Both paper forms are converted into electronic format through completion of electronic forms that are designed to not allow manual text entry (i.e. only radio button selection) in order to ensure data accuracy during transfer. All data is then stored electronically on password-protected shared drives and backed up weekly to a password-protected folder on the University of Adelaide’s network. All hard-copy questionnaire and consent forms are stored in locked compactus storage requiring key-card access. Only investigators will have access to the data.

### Sample size

This study has been designed as a pilot study to determine the feasibility of a large-scale RCT. Therefore, no sample size calculation was performed. Based on the number of fractures in a year at the recruitment sites, we aim to recruit a total of 60 patients; allowing for some loss to follow-up, should enable 25 patients to complete follow-up assessments from each group (SPN and IPN), which is in-line with sample size recommendations for pilot studies [72].

### Statistical analysis

Enrolment rates will be calculated as the ratio between the number of enrolled participants and the total number of eligible patients presenting at the enrolment sites. Retention rates will be determined by the total number of enrolled participants completing their 18-month follow-up appointment. Compliance with questionnaire and assessment procedures will be assessed by analysing the completion rates of all questionnaires and assessments (e.g. radiographs and MRI). All adverse events will be recorded and the total number and impact of all adverse events rated on a single 7-point Likert scale ranging from 0 to 6, with 6 indicating no impact from adverse events. See Table 2 for a description of feasibility outcome metrics and progression criteria based on the traffic light system [73]:

**Table 2 Tab2:** Feasibility outcome metrics and traffic light system progression criteria

Outcome	Red: major revision prior to full trial	Amber: continue to full trial with changes	Green: continue to full trial without changes
Enrolment rate (target: 60 enrolled after 18 months)	< 60 % of eligible patients enrolled	60–80% of eligible patients enrolled	> 80% of eligible patients enrolled
Retention rate	< 70% complete 18-month follow-up	70–80% complete 18-month follow-up	> 80% complete 18-month follow-up
Questionnaire and assessment compliance	< 80% completion of all questionnaires and assessments	80–90% completion of all questionnaires and assessments	> 90% completion of all questionnaires and assessments
Adverse events	Score of < 3 on a 7-point Likert scale indicating total impact of all adverse events	Score of 3 or 4 on a 7-point Likert scale	Score of ≥ 5 on a 7-point Likert scale.

Green: continue to full trial without changes

Amber: continue to full trial with changes to the protocol as deemed necessary by the Trial Steering Committee relating to enrolment rate, retention rate, questionnaire and assessment compliance, and the occurrence of any adverse events

Red: do not continue to full trial. Major revisions to the protocol are required. Trial Steering Committee to determine whether the study warrants continuing even with major revisions

As this is a pilot study, any analyses related to the clinical outcomes should be treated with caution and viewed as exploratory. All clinical outcome measures will be assessed descriptively (means and standard deviations for normally distributed continuous variables; medians and interquartile ranges for non-normal continuous variables; frequencies and percentages for categorical variables). Missing data will be tabulated.

Logistic regression models will be used to determine the association between surgical approach and AKP 12 months post-surgery. Models will be adjusted for age and gender with hospital included as a fixed effect. The results will be reported as odds ratios with 95% confidence intervals.

Secondary clinical outcomes will be analysed using linear regression models for continuous outcomes or generalised linear models for count or categorical outcomes. Generalised estimating equations will be used to account for correlation due to repeated measures over time, and a time-by-surgery interaction term will be included to test for differences in the relationship between surgical approach and outcomes over time. If assumptions about distributions are not met (e.g. non-normally distributed continuous outcomes) alternative approaches will be explored as appropriate, including transformations or non-parametric modelling.

To assess differences between cases and matched healthy controls, logistic regression models will be used to determine the association between treatment (surgery versus no surgery) and AKP 12 months post-surgery. Models will be adjusted for the matching variables age, gender, and body mass index, with hospital also included as a fixed effect.

To determine novel predictors of functional outcomes, logistic regression prediction models will be used to assess the discriminatory power of PROMs and PBOMs at assessing AKP and other functional measures. Estimates of discrimination (area under the curve, sensitivity, and specificity) will be used to rank combinations of outcomes in ability to predict AKP. Principal component analysis (PCA) will be explored as a method of data reduction to allow information from a larger number of variables to be included in the predictive model. If PCA is successful, a predictive model will be fitted using an appropriate number of principal components (determined using the proportion of variance explained as well as number of events in the dataset) as predictors.

For all outcomes, effect estimates and 95% confidence intervals will be reported to express uncertainty about the estimated effects.

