The results of this pilot study will help inform the design of a large-scale RCT. Progression criteria, using the traffic light system, relating to the feasibility outcome metrics presented in Table 2, will inform the definitive trial: if all metrics are green, continue to the full trial; if any metrics are amber, continue to the full trial with appropriate modifications to the protocol as determined by the Trial Steering Committee; if any metrics are red, do not continue to the full trial as major revisions to the trial protocol are required before continuing, or the trial should not continue. Further, this study will explore the development of novel, biomechanically validated outcome measures for AKP and knee function and aid in the development of a new tool for assessing AKP in this cohort. Any clinical outcomes between approaches should be treated with caution due to the small sample size (*n* = 60). However, these outcomes may provide information to help inform the design of the full-scale RCT by providing preliminary effect sizes and more accurate power calculations. In addition to the small sample size, other limitations include an unpredictable enrolment rate and loss to follow-up and the unknown ability of 3-D motion analysis to pick up the effects of AKP after tibial nailing. If there is substantial uncertainty and areas of concern about the feasibility of a future definitive RCT, then the protocol will be revised.

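### The enrolment traffic light carries a target of 60 in 18 months that none of its cut-offs uses, so it can show green while recruitment falls well short

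*Protocol article*

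**What the plan says.** Feasibility of a full-scale trial is the primary objective, and the Statistical analysis section of the protocol article sets out how it will be judged. Enrolment is defined there as "the ratio between the number of enrolled participants and the total number of eligible patients presenting at the enrolment sites". In Table 2 the row for this metric is headed "Enrolment rate (target: 60 enrolled after 18 months", which is a count over a period. The cut-offs in the same row are "< 60 % of eligible patients enrolled" for red, "60–80% of eligible patients enrolled" for amber and "> 80% of eligible patients enrolled" for green.

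The Discussion says what the lights decide: "if all metrics are green, continue to the full trial". It also says "if any metrics are red, do not continue to the full trial as major revisions to the trial protocol are required before continuing".

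The Sample size section derives the 60 from the yearly fracture volume at the two hospitals, without giving that volume. It expects 25 patients per group to complete follow-up.

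**The concern.** The label and the cut-offs of one row measure different things. The label asks whether 60 patients were recruited in 18 months. The cut-offs ask what share of the eligible patients was recruited. The share does not depend on how many eligible patients turn up, so it says nothing about the pace of recruitment.

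Pace matters to the primary objective. A definitive trial needs enough patients in a workable time, and the number of sites and the duration are planned from the recruitment rate seen in the pilot. If the hospitals see fewer eligible fractures than expected but most of those patients agree, the enrolment light is green. With the other metrics green as well, the stated rule is to go ahead without changes, on a pilot that missed its own recruitment target.

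**Working it through.** **Inputs from the protocol article.** Target: 60 by month 18 (Table 2). Metric: enrolled / eligible (Statistical analysis). Cut-offs: below 60% red, 60–80% amber, above 80% green (Table 2). Completers expected: 25 per group (Sample size).

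**Input not given.** The number of eligible patients in 18 months is not stated. The values below are assumptions.

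**The plan's own figure.** The 60 has no formula behind it, because the protocol states that no sample size calculation was done. It can only be checked against the completers: 2 × 25 = 50, and 50/60 = 83.3%, an implied loss of 10/60 = 16.7%. That is internally consistent.

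**Smallest enrolment that turns the light green.** For E eligible patients this is the smallest whole number e with e/E > 0.80. It is compared with the target as e/60. At that pace, the time to reach 60 is 60 / (e/18) months.

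| Eligible by month 18 (assumed) | Smallest green enrolment | Share of eligible | Share of 60 | Months to reach 60 |
|---|---|---|---|---|
| 20 | 17 | 85.0% | 28% | 64 |
| 30 | 25 | 83.3% | 42% | 43 |
| 40 | 33 | 82.5% | 55% | 33 |
| 50 | 41 | 82.0% | 68% | 26 |
| 60 | 49 | 81.7% | 82% | 22 |
| 70 | 57 | 81.4% | 95% | 19 |
| 73 | 59 | 80.8% | 98% | 18.3 |
| 74 | 60 | 81.1% | 100% | 18 |

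**Boundaries.** With 73 eligible, 0.80 × 73 = 58.4, so 59 enrolled is already green. With 74 eligible, 0.80 × 74 = 59.2, so green needs 60. Green therefore guarantees the target only from 74 eligible upwards. Below 60 eligible the target cannot be met even if everyone enrols, yet green remains possible.

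**Effect on completers.** At the implied loss of 16.7%, 33 enrolled would give 33 × 50/60 = 27.5 completers in total, against the 50 expected.

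**The case against.** The share of eligible patients enrolled is a legitimate feasibility measure. It speaks to acceptability and selection, and the pilot would be poorer without it. That stands, and the fix keeps it.

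The rule is also less mechanical than Table 2 alone suggests. The Discussion closes by allowing the protocol to be revised where there is serious doubt about feasibility, and the number enrolled will be known in any case. Recruiting 33 of 60 could well prompt such a revision. This lowers the severity but does not close the gap: the provision names no metric and no threshold, while the rule stated in advance still says to continue when all lights are green.

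Three stronger readings are tempting, and the document does not support them.

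- A reader might infer that the light is equally wrong in the other direction. With exactly 60 enrolled it is green for 60–74 eligible, amber for 75–100 and red from 101 (60/101 = 59.4%). But enrolling under 60% of eligible patients is a fair warning about acceptability or selection even when the count is reached. Red also refers the question of major revision to the Trial Steering Committee; it is not a final stop.
- A reader might take the limitation about unpredictable enrolment as an admission that the number of patients presenting is uncertain. The protocol defines its enrolment rate as the proportion, so the remark does not speak to patient supply.
- A reader might project the target pace onto the 1080 patients mentioned in the Discussion. That figure illustrates why a binary pain outcome is costly. It is not the planned size of the definitive trial.

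**Conclusion.** The concern holds in one direction. The enrolment row states a target by count and time, and the progression rule uses neither. Green is compatible with a missed target at any eligible number up to 73; at an assumed 40 eligible, the light is green with 55% of the target recruited.

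The mismatch itself rests on the text alone. Its size in practice depends on the number of eligible patients, which the article does not give, so the likelihood of a misleading green light cannot be judged from the document.

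This should be fixed because it bears on the decision that serves the primary objective. It is not a fatal flaw: no analysis of treatment effect is affected, and the investigators retain discretion to revise the protocol.

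**What to change.** Split the enrolment row of Table 2 in two.

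1. **Proportion of eligible patients enrolled**, with the present definition and thresholds.
2. **Number randomised by month 18**, against 60. The sponsor should set the cut-offs in advance and justify them against the 50 completers, with green at or near 60. The 60% and 80% cut-points should not be carried over. On a target of 60 they fall at 36 and 48, so 49 enrolled would be green with the target still missed, and 49 × 50/60 gives about 41 completers.

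Also report patients recruited per site-month with a 95% confidence interval, for planning the definitive trial. The target itself amounts to 60/18 = 3.33 per month, or 60/36 = 1.67 per site-month on average if both hospitals recruit throughout.

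The cost is one table row. The count of enrolled patients is already the numerator of the existing ratio; only the recruiting months per site need to be noted. The downside is one more metric that can turn amber or red. The cut-offs should be fixed before recruitment figures are reviewed, since thresholds chosen afterwards would carry little weight.
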